## Abstract

**Background:**

Retained placenta is one of the common causes of maternal mortality in developing countries where access to appropriate obstetrical care is limited. Current treatment of retained placenta is manual removal of the placenta under anaesthesia, which can only take place in larger health care facilities. Medical treatment of retained placenta with prostaglandins E1 (misoprostol) could be cost-effective and easy-to-use and could be a life-saving option in many low-resource settings. The aim of this study is to assess the efficacy and safety of sublingually administered misoprostol in women with retained placenta in a low resource setting.

**Methods:**

Design: Multicentered randomised, double-blind, placebo-controlled trial, to be conducted in 5 hospitals in Tanzania, Africa.

Inclusion criteria: Women with retained placenta, at a gestational age of 28 weeks or more and blood loss less than 750 ml, 30 minutes after delivery of the newborn despite active management of third stage of labour.

Trial Entry & Randomisation & Study Medication: After obtaining informed consent, eligible women will be allocated randomly to the treatment groups using numbered envelopes that will be randomized in variable blocks containing identical capsules with either 800 microgram of misoprostol or placebo. The drugs will be given sublingually. The women, maternal care providers and researchers will be blinded to treatment allocation.

Sample Size: 117 women, to show a 40% reduction in manual removals of the placenta (p = 0.05, 80% power). The randomization will be misoprostol: placebo = 2:1

Primary Study Outcome: Expulsion of the placenta without manual removal. Secondary outcome is the number of blood transfusions.

**Discussion:**

This is a protocol for a randomized trial in a low resource setting to assess if medical treatment of women with retained placenta with misoprostol reduces the incidence of manual removal of the placenta.

**Clinical Trial Registration:**

Current Controlled Trials ISRCTN16104753

## Background

### Retained placenta: diagnosis, definition and the burden of disease

The diagnosis 'retained placenta' (RP) is established when the placenta is not expelled after a certain time period following the delivery of the infant[1,2]. The time period in the definition of RP varies among countries. In our study location Tanzania, like most English speaking countries, RP is defined as lack of expulsion of the placenta 30 minutes after delivery of the infant [3], while in other countries the diagnosis RP is only made after 60 minutes postpartum [4]. Complications of RP are postpartum haemorrhage and infection[5], which may both lead to maternal morbidity and mortality. The need to improve maternal mortality has been recognized at a global level by including it in the Millennium Development Goals [6].

Tanzania is a low resource country with a high maternal mortality rate. It is estimated that 578 women per 100,000 live-births die as a result of pregnancy-related complications [7]. A retrospective study in Tanzania showed that RP contributed by 13% to the maternal deaths [8]. The morbidity due to RP is mainly caused by infections and anaemia. A study by Tandberg et al found a significant fall in haemoglobin level postpartum compared to antepartum by a mean of 3.4 g/dl (2.1 mmol/l) in the RP group as compared to no significant change in the controls; blood transfusion was required in 10% of the RP group versus 0.5% in the control group [9].

### Retained Placenta: incidence

The incidence of RP is approximately 1-2% of all deliveries worldwide, the exact data for Tanzania is not known. The reported incidence of RP is affected by the following four factors: definition of the time interval [4], gestational age, an obstetrical history of previous RP or not, and the presence or absence of active management of the third stage of labour (AMTSL).

The incidence of RP in an unselected group of nulliparous women in The Netherlands was 6.3% at 30 minutes and 1.8% at 60 minutes after delivery of the newborn [4]. The incidence of RP, 30 minutes after delivery of the newborn has been reported as 8% in preterm and 1.1% in term deliveries [10]. The recurrence risks of RP reported in two studies of parous women were 16% and 23% [9,11]. A randomized controlled trial (RCT) showed that AMTSL reduced the incidence of RP (after 30 minutes) to 1.6% as compared to 4.6% in the control group [12].

### Retained placenta: how can we prevent maternal mortality?

Blood loss associated with RP can be acute life-threatening and requires emergency interventions like administration of uterotonics, correction of hypovolaemia by administration of intravenous fluids, manual removal of the placenta (MRP) under anaesthesia and blood transfusions[13]. All these interventions need skilled personnel and equipment. In many low-resource countries women deliver at home, and the nearest health care facility often lacks drugs and equipment to perform MRP or to give blood transfusion, leaving the midwife empty-handed. Transport to health care facilities with comprehensive emergency obstetrical care requires time and money, both are limited commodities in those circumstances [6,8]. Medical treatment of RP with an easy-to-administer drug could save the life of patients under those circumstances.

### Retained placenta: medical treatment with prostaglandin analogues

Medical treatment of RP includes the administration of oxytocin in the umbilical vein, which was reported to be effective in one out of eight women (relative risk 0.79, 95% CI 0.69-0.91) [14]. The disadvantage of this method in low resource settings is that it requires skilled medical personnel and equipment.

A RCT in The Netherlands showed that administration of 250 microgram prostaglandin E2 (sulprostone) intravenously 60 minutes after delivery of the infant effectively expelled 49% of RP versus 11% in the placebo group [15] within 60 minutes after administration. Blood loss was 388 ml lower in the sulprostone group (average blood loss 1062 ml) as compared to controls (average blood loss 1450 mls). Unfortunately, treatment with sulprostone is not applicable in low resources settings because the drug is relatively expensive and needs to be stored refrigerated.

The prostaglandin E1 analogue misoprostol is inexpensive and does not need to be stored refrigerated. Therefore, it is of potential use in low-resource countries. In a recent study in which 54 patients with RP were randomised to misoprostol, oxytocin and placebo, administered through the umbilical cord [16], a significant reduction of MRP was reported for the misoprostol (43% MRP) compared to the oxytocin (80% MRP) and placebo (54% MRP) groups. When misoprostol was administered rectally in a group of 10 patients [17], it was reported to avoid MRP in 7 patients and to reduce blood loss. Oral or sublingual administration of misoprostol, though potentially the fastest acting [18] and most practical, has not been studied in an effort to reduce MRP.

### Misoprostol

Misoprostol is an prostaglandin E1-analogue with uterotonic properties that can be administered orally, sublingually, vaginally and rectally [19]. Sublingual administration of misoprostol achieves the highest serum peak concentration and takes the shortest time to reach the peak level, in comparison with other routes of administration [18]. Misoprostol is cheap and stable at room temperature. Originally, misoprostol was introduced as treatment for peptic ulcers. It soon became obvious that it stimulates uterine contractions [20]. Misoprostol has been used to treat various obstetrical problems, including uterine atony, postpartum haemorrhage [21], induction of labour, and induction of abortion [19,20]. Misoprostol when given postpartum is known to cause only mild side effects (shivering and pyrexia) [19,22-24]. Misoprostol is a sustainable drug for use in developing countries for the treatment of various obstetrical complications [20] like postpartum haemorrhage, induction of labour and induction of abortion. It is registered in Tanzania for the prevention and treatment of postpartum haemorrhage.

### Study justification

Women in rural areas in resource-poor settings who deliver at home or in a village health care facility, and in whom the delivery is complicated by RP, have difficulty to reach appropriate medical help in time and have a considerable chance to die because from post partum hemorrhage. Because preliminary evidence suggests that prostaglandins like misoprostol may expel the placenta and reduce blood loss in women with RP, a RCT is designed to compare sublingually administered misoprostol with placebo to tests its effectiveness to reduce the need of MRP and blood transfusion in a low-resource setting.

### Aims of the trial

The aims of this randomised, double blind, placebo-controlled trial is to assess if sublingual misoprostol reduces the need of Manual Removal of Placenta (MRP) and the amount of blood loss in women with RP in a low resource setting. The primary outcome variable is reduction in the incidence of MRP and the secondary outcome variable is the reduction in the number of units of packed cells administered.

The primary hypothesis of this randomised trial is that the administration of misoprostol to women with RP reduces the number of women who need MRP. The secondary hypothesis is that misoprostol reduces the amount of blood loss in women with RP, especially in those in whom the placenta is expelled by the intervention. Since measurement of blood loss during delivery is not always very reliable, we choose as secondary outcome variable both the measured amount of blood loss and the number of administered packed cells.

## Methods/Design

### Study Design

Multicentered randomised, double-blind, placebo-controlled trial.

### Participating hospitals & approval

The study will be conducted in four rural hospitals in Southern Tanzania (the regional hospitals of Lindi and Mtwara regions and Ndanda and Nyangao mission hospitals) and in the university teaching hospital in the capital Dar es Salaam. Approval for this study was obtained from the National Institute of Medical Research (NIMR), the Senate Research and Publication Committee of Muhimbili University of Health and Allied Sciences and the Muhimbili National Hospital in Tanzania. A data management safety board has been installed.

### Inclusion criteria and trial entry

All labouring women will receive AMTSL and are eligible if 30 minutes after delivery of the infant the placenta has not been expelled and were delivered of a baby of 1 kg or more or at a gestational age of 28 weeks or more. AMTSL is defined as administration of 5IU oxytocin and controlled cord traction (CCT). If the placenta is delivered the uterus will be massaged.

### Exclusion criteria

Women with one of the following conditions will be excluded from entering the trial:

• Haemoglobin concentration less than 100 g/l (6.2 mmol/l)

• Blood loss more than 750 ml

• Pulse rate more than 120 beats per minute

• Diastolic blood pressure reduction after delivery more than 20 mmHg

### Trial Entry

Eligible women will be identified in the labour ward at 20 minutes after delivery of the infant. The bladder will be catheterised, an intravenous canula will be inserted and normal saline solution will be started, CCT will be performed again and blood will be taken for cross-match and haemoglobin concentration. They will receive verbal and written information in Kiswahili about participation in the trial and will be asked to give their informed consent. The randomisation schedule uses balanced variable blocks; sealed envelopes containing both registration form and blinded study medication are present in the delivery room. Allocation will be in sequence of enrolment in each of the five labour wards. Each sealed envelop contains two identical capsules with either 800 microgram misoprostol or placebo. The patient, the maternal care providers and the researchers are all blinded to the allocation. Women will enter the study after giving their informed consent at 30 minutes following the delivery of the infant, at which time the envelope will be opened and the two capsules of study medication will be administered sublingually. Figure 1 depicts the flowchart for trial entry.

**Figure 1 F1:**
[figure not shown]
**Flowchart for trial entry**. AMTSL = Active management of third stage of labour. RP = retained placenta. CCT = controlled cord traction. Hb = Haemoglobin. BP = Blood pressure. MRP = Manual removal of placenta. Hb = haemoglobine.

### Study Medication & Treatment Schedules

After administration of the study medication, the doctor or midwife will perform CCT every ten minutes to check if the placenta has separated from the uterine wall. Vaginal blood loss will be measured by weighing self absorbable mattresses. Blood loss exceeding 1500 ml will be considered as indication for emergency MRP. If the placenta is not expelled 30 minutes after the administration of the study medication, the patient will undergo MRP.

### Follow-up of women in both treatment groups

All women enrolled in the study are followed up for 12-24 hours. Blood pressure, pulse rate uterine contraction and vaginal blood loss are monitored, and the haemoglobin concentration prior to discharge is recorded. Women are receiving blood transfusion and and/or intravenous iron dextrane infusion, according to the hospitals guidelines, if needed. All women receive combined ferrofumerate and folic acid tablets according to the national guideline on care for post partum women.

### Study Endpoints

The primary study outcome is:

• Manual removal of the placenta.

The secondary outcomes are:

• Measured post partum blood loss,

• Number of units of blood administered,

• Adverse outcome for the woman, including side-effects from the study medication and number of emergency MRP needed.

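### Read literally, the secondary blood-loss endpoint includes up to 750 ml lost before the study drug, and the stated analysis makes no use of loss at entry: a modest, avoidable loss of precision

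*Protocol article*

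**What the plan says.** All references are to the protocol article.

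- **Hypothesis** (Aims of the trial): "The secondary hypothesis is that misoprostol reduces the amount of blood loss in women with RP". The same section concedes that blood-loss measurement is imperfect and pairs it with the number of packed cells given.
- **Endpoint** (Study Endpoints): "Measured post partum blood loss". Neither a start nor a stop is given.
- **Entry limit** (Exclusion criteria): "Blood loss more than 750 ml". The abstract dates the assessment: "blood loss less than 750 ml, 30 minutes after delivery of the newborn".
- **Time of dosing** (Trial Entry): "Women will enter the study after giving their informed consent at 30 minutes following the delivery of the infant". The capsules are given at that moment.
- **Measurement** (Study Medication & Treatment Schedules): "Vaginal blood loss will be measured by weighing self absorbable mattresses". This sentence stands in a paragraph that begins with what happens once the drug has been given.
- **End of observation** (Follow-up of women in both treatment groups): "All women enrolled in the study are followed up for 12-24 hours".
- **Analysis** (Analysis and Reporting of Results): relative risks with 95% confidence intervals for primary and secondary outcomes, by intention to treat, plus a check of baseline differences. Loss at entry is not mentioned.

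**The concern.** If the outcome runs from birth, each woman's value is the sum of two parts: loss in the first 30 minutes, before randomised treatment, and loss afterwards. Only the second part can respond to misoprostol. The first part adds variance, and any chance difference between the arms in it passes unchanged into an unadjusted comparison of total loss.

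The first part is also a baseline quantity. It must be judged against 750 ml before a woman can be enrolled, so it could be used to sharpen the comparison. The stated analysis does not use it.

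What is at stake is the precision of the direct measure of the secondary hypothesis, in a trial of 39 versus 78 women. The primary outcome, manual removal of the placenta, is not affected.

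**Working it through.** **The plan's own figure.** There is none to reproduce. The Sample Size section concerns manual removal only, and no SD, target difference or power is given for blood loss. From that section I take only the arm sizes, 39 placebo and 78 misoprostol.

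**Assumed inputs.**
- SD of loss at entry: 100 to 217 ml. The upper value is a uniform spread over 0 to 750 ml: 750/√12 = 217. This is wide, and nothing in the documents supports it over a narrower spread.
- SD of loss after dosing: 300 to 600 ml.
- Correlation ρ between the two: 0, with 0.3 as a sensitivity case.

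**1. Variance of total loss.** With ρ = 0, Var(total) = SDpre² + SDpost². Analysing loss from dosing, or adjusting for entry loss, leaves SDpost². The gain, as a fraction of extra women, is SDpre²/SDpost².

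| SDpre | SDpost | Pre-drug share of total variance | Equivalent extra women |
|---|---|---|---|
| 217 | 300 | 47,089/137,089 = 34% | 47,089/90,000 = 52% |
| 217 | 600 | 47,089/407,089 = 12% | 47,089/360,000 = 13% |
| 100 | 300 | 10,000/100,000 = 10% | 10,000/90,000 = 11% |
| 100 | 600 | 10,000/370,000 = 3% | 10,000/360,000 = 3% |

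The range is therefore 3% to 52%.

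**2. Power.** For a true difference of 200 ml (assumed), 39 versus 78 women, two-sided 5%. SD(total) = √(SDpre² + SDpost² + 2ρ·SDpre·SDpost); the residual SD after adjustment for entry loss is SDpost·√(1 − ρ²).

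| SDpre / SDpost | ρ | Total loss | Loss from dosing | Adjusted for entry loss |
|---|---|---|---|---|
| 217 / 300 | 0 | 79% | 93% | 93% |
| 100 / 600 | 0 | 39% | 40% | 40% |
| 217 / 300 | 0.3 | 68% | 93% | 95% |
| 100 / 600 | 0.3 | 36% | 40% | 43% |

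Against loss from dosing, unadjusted total loss costs about 1 to 14 points of power at ρ = 0 and 4 to 24 points at ρ = 0.3.

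**3. Chance imbalance.** The standard error of the difference in mean entry loss is SDpre × √(1/39 + 1/78) = 0.196 × SDpre, or 20 to 43 ml. The 95% range is ±1.96 times this, about ±38 to ±83 ml, and it enters an unadjusted difference in total loss in full.

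**4. Bias.** E[difference in total] = E[difference in entry loss] + E[difference in post-drug loss]. Randomisation makes the first term zero, so total loss and loss from dosing estimate the same mean difference. In a linear model with entry loss as covariate, the treatment coefficient is identical whichever of the two is the outcome, because they differ only by the covariate.

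**The case against.** Several counter-arguments have force.

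- **Total loss from birth is not stated.** A reader might infer that the document fixes the endpoint that way. It does not. The only account of measurement follows the reference to giving the drug, so measurement from dosing remains possible, and then there is nothing to remove. The emergency threshold does not settle it either: "Blood loss exceeding 1500 ml will be considered as indication for emergency MRP" names no starting point. This stands. The claim is limited to the literal reading and an unsettled start.
- **The entry value may not exist as a volume.** A reader might infer that it is already on file and free to use. Eligibility needs only a classification against 750 ml. Subtracting a rough visual estimate from a weighed total could add error. This stands, and it is why the fix asks for a weighing at dosing and makes covariate adjustment the core step.
- **There is no bias.** A reader might infer that the unadjusted comparison is invalid. It is valid, and total loss is a legitimate clinical measure. This stands.
- **Model details belong in an analysis plan or full protocol not shown here.** This holds for the covariate list: its absence from an article is not an error. It does not hold for the start of measurement. If loss is not separated at dosing, no later plan can recover the split.
- **The size is assumed.** A reader might quote only the 13% to 52% that follows from a uniform entry loss. With SD 100 ml the gain is 3% to 11%. The one blood-loss effect in the article, 388 ml with sulprostone (another drug, given at another time), would leave little to gain: with entry SD 217 and post-drug SD 600, power is about 91% for loss from dosing against 87% for total loss. This stands, and the verdict uses the wide range.
- **Packed cells are a companion outcome.** True, but blood loss itself remains the direct measure of the hypothesis.

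**Conclusion.** The point holds as a modest gain in precision on a secondary endpoint. On the ordinary meaning of post partum, the endpoint includes up to 750 ml lost before dosing, and the stated analysis makes no use of that loss. If measurement in fact starts at dosing, the endpoint is misnamed and the wording needs correcting instead.

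Removing or adjusting for entry loss is worth roughly 3% to 52% more women for this endpoint. This rests on assumed SDs of 100 to 217 ml at entry and 300 to 600 ml after dosing, taken as independent. A positive correlation would increase the gain from adjustment. The low end is negligible; the high end needs a wide spread at entry and a fairly narrow one afterwards. The documents cannot say where in this range the trial lies. The change is worth making because it is cheap, not because the planned comparison is wrong.

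**What to change.** 1. In Study Endpoints, state when blood-loss measurement starts.
2. Weigh or change the mattress at dosing and record the measured loss at that time as a number for every woman.
3. Analyse blood loss as a continuous outcome, with loss at entry as a covariate. Total loss and loss from dosing then give the same treatment effect. Hospital as a further covariate is optional.
4. Keep total post-partum loss as a descriptive measure by arm.

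**Cost:** one extra weighing and one recorded value per woman, and one covariate in the model. The weighing falls at a busy moment on the labour ward, so it is not free, but it also documents the 750 ml eligibility check. The sample size and the primary analysis do not change.

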### Sample Size

The primary endpoint of the study is manual removal of the placenta. For eligible women (with RP 30 minutes after delivery of the infant) the best estimate of MRP is 44% at 60 minutes post partum. Using 2:1 misoprostol to placebo randomisation, a sample size of 117 women will be able to show a 40% reduction in MRP (5% level of significance, two-tailed alpha, 80% power). Thus, 39 patients will receive placebo and 78 will receive misoprostol.

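### The stated inputs do not give 117 women: with 44% MRP on placebo, 39 against 78 women have about 48% power for a 40% reduction, not 80%

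*Protocol article*

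**What the plan says.** The Sample Size section of the protocol article sets out a complete calculation.

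- Endpoint: "The primary endpoint of the study is manual removal of the placenta".
- Event rate without active treatment: "the best estimate of MRP is 44% at 60 minutes post partum".
- Allocation: "Using 2:1 misoprostol to placebo randomisation".
- Effect, total and error rates: "a sample size of 117 women will be able to show a 40% reduction in MRP (5% level of significance, two-tailed alpha, 80% power".
- Arms: "Thus, 39 patients will receive placebo and 78 will receive misoprostol".

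The Methods part of the abstract repeats the claim: "117 women, to show a 40% reduction in manual removals of the placenta (p = 0.05, 80% power". Neither place gives another control rate, a dropout allowance or a one-sided test for this calculation. The section on analysis and reporting plans relative risks with 95% confidence intervals, by intention to treat.

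**The concern.** Every input needed to check the sample size is stated, and the total looks too small for them. A drop of 17.6 percentage points from a rate near one half is not usually detectable with 39 women in the smaller arm.

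This is the only justification given for the size of the trial, and it concerns the primary endpoint. If the power is overstated, a non-significant result could be read as showing that misoprostol does not work, because the trial was described as having 80% power. The Discussion says a positive result should change basic obstetric care in rural health centres, so a false negative would also carry weight.

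**Working it through.** **Inputs (Sample Size section).** Placebo MRP rate p0 = 0.44; 40% reduction; k = 2 misoprostol women per placebo woman; two-sided 5% (z = 1.960); 80% power (z = 0.842); n0 = 39, n1 = 78.

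**Step 1. Try to reproduce 117, reading the reduction as relative.**
p1 = 0.44 × 0.60 = 0.264; difference d = 0.176; weighted mean p̄ = (0.44 + 2 × 0.264)/3 = 0.3227.

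Pooled-variance formula for the placebo arm:

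n0 = [1.960 × √(p̄(1−p̄)(1 + 1/k)) + 0.842 × √(p0(1−p0) + p1(1−p1)/k)]² / d²

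= [1.960 × 0.5726 + 0.842 × 0.5861]² / 0.176² = 84.3, so 85 placebo + 170 misoprostol = **255**.

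Other versions:
- Unpooled variance: 87.1, total 264.
- Continuity correction: 92.6, total 279.
- One-sided 5%, contrary to the text: 201.
- 1:1 allocation, contrary to the text: 115 per arm, total 230.

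None gives a total of 117.

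**Step 2. Read the reduction as 40 percentage points.**
44% to 4% needs 36 women (pooled) or 42 (unpooled). With 39 and 78, power exceeds 99%. This does not give 117 either.

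**Step 3. Power of the planned design for 44% against 26.4%.**
Standard error under no difference: √(0.3227 × 0.6773 × (1/39 + 1/78)) = 0.0917.
Standard error under the planned effect: √(0.44 × 0.56/39 + 0.264 × 0.736/78) = 0.0939.
Power = Φ[(0.176 − 1.960 × 0.0917)/0.0939] = Φ(−0.039) = **48.4%**.

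| Test | Power at 39/78 |
|---|---|
| z test, pooled variance | 48.4% |
| z test, unpooled variance | 46.6% |
| Chi-square, exact enumeration | 49.3% |
| Fisher's exact | 42.6% |

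**Step 4. What 39 and 78 women can detect.**
With 44% on placebo, power reaches 80% (pooled) only when the misoprostol rate falls to about 0.192. That is a reduction of 24.8 points, or 0.248/0.44 = 56% relative.

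**Step 5. Precision at exactly the planned effect.**
SE of log RR = √(0.56/(39 × 0.44) + 0.736/(78 × 0.264)) = 0.261. So RR = 0.60, with 95% CI 0.60 × exp(±1.96 × 0.261) = 0.36 to 1.00. A trial that observed precisely the planned effect would sit on the border of significance.

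**Step 6. Which inputs would give about 117?**
- Placebo rate 66%, 40% relative reduction (66% to 39.6%), unpooled: 38.7, rounded up to 39; total 117.
- Placebo rate 68%, same reduction, pooled: 38.6, rounded up to 39; total 117.
- Placebo rate 44% reduced *to* 40% of itself (17.6%), continuity-corrected: 39.2, or 117.6 in total before rounding (120 if the arm is rounded up).
- 117 taken per arm at 1:1 for 44% against 26.4%: 80.9% power.

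Each contradicts something in the Sample Size section.

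**The case against.** The strongest reply is that the inconsistency does not prove the design is underpowered. The 48% applies only if 44% is the true placebo rate and the true effect is a 40% relative reduction. The slip may lie in the wording of the effect. If the intended calculation was a fall to 40% of the control rate (44% to 17.6%), then 39 and 78 women have about 83% to 85% power. A placebo rate of 66% to 68% also fits the total, but neither figure appears in the document, and which one fits depends on the variance formula. Choosing among these is conjecture.

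That part stands: the protocol alone does not show which input went wrong. It does not rescue the text. Under every reading tried, at least one published figure has to change, and nothing in the document says which.

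The background cites other results from which placebo MRP rates could be inferred: 1.8/6.3 = 29% persistence between 30 and 60 minutes in Dutch nulliparous women, 54% MRP after umbilical placebo, and 89% after intravenous placebo (100% less 11% expelled). Power for a 40% relative reduction would then be 31%, 62% and 99%. These come from different populations, routes and time windows. They show only how strongly power depends on the placebo rate and do not estimate that rate for this trial.

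The article form is no defence. A condensed article may omit detail, but this one states all the inputs, and they contradict the result.

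**Conclusion.** The point holds. With the inputs as published, 117 women at 2:1 give about 48% power (43% to 49% by test) in place of the stated 80%, and 80% power would need about 255 women, more than twice the planned number. This rests on two natural readings: that 44% is the placebo rate, and that the 40% is relative, in line with the planned relative risks. The absolute reading does not give 117 either. The sample-size statement is therefore wrong as written. What cannot be settled from the document is whether the 44%, the 40% or the 117 is the faulty figure.

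**What to change.** Correct the Sample Size section and the Methods part of the abstract together, in one of these ways:

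- **Keep 44% and 117.** State that 39 + 78 women give about 48% power for 44% to 26.4%, and 80% power only for a fall to about 19% (a relative reduction of about 56%).
- **Correct the input.** If 117 was computed from another placebo rate or another effect, state that figure and its source in place of the one printed, and name the formula.
- **Correct the number.** If 44% and a 40% relative reduction are both intended with 80% power, recalculate: 85 + 170 = 255 women, or 279 with continuity correction.

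In each case say that the reduction is relative. Add a sentence that a non-significant result will be interpreted from the confidence interval and not as evidence of no effect.

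The first two cost a rewording of one paragraph and one line of the abstract, with no extra patients; the first also means a less favourable power statement. The third means 138 more women (255 − 117), so it is a decision for the sponsor and not a condition of correcting the text.
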